## Abstract

**Background:**

Women with a history of gestational diabetes mellitus (GDM) are 12-fold more likely to develop type 2 diabetes (T2D) 4–6 years after delivery than women without GDM. Similarly, GDM is associated with the development of common mental disorders (CMDs) (e.g. anxiety and depression). Evidence shows that holistic lifestyle interventions focusing on physical activity (PA), dietary intake, sleep, and mental well-being strategies can prevent T2D and CMDs. This study aims to assess the effectiveness of a holistic lifestyle mobile health intervention (mHealth) with post-GDM women in preventing T2D and CMDs in a community setting in Singapore.

**Methods:**

The study consists of a 1-year randomised controlled trial (RCT) with a 3-year follow-up period. Post-GDM women with no current diabetes diagnosis and not planning to become pregnant will be eligible for the study. In addition, participants will complete mental well-being questionnaires (e.g. depression, anxiety, sleep) and their child’s socio-emotional and cognitive development. The participants will be randomised to either Group 1 (Intervention) or Group 2 (comparison). The intervention group will receive the “LVL UP App”, a smartphone-based, conversational agent-delivered holistic lifestyle intervention focused on three pillars: Move More (PA), Eat Well (Diet), and Stress Less (mental wellbeing). The intervention consists of health literacy and psychoeducational coaching sessions, daily “Life Hacks” (healthy activity suggestions), slow-paced breathing exercises, a step tracker (including brisk steps), a low-burden food diary, and a journaling tool. Women from both groups will be provided with an Oura ring for tracking physical activity, sleep, and heart rate variability (a proxy for stress), and the “HAPPY App”, a mHealth app which provides health promotion information about PA, diet, sleep, and mental wellbeing, as well as display body mass index, blood pressure, and results from the oral glucose tolerance tests. Short-term aggregate effects will be assessed at 26/27 weeks (midpoint) and a 1-year visit, followed by a 2, 3, and 4-year follow-up period.

**Discussion:**

High rates of progression of T2D and CMDs in women with post-GDM suggest an urgent need to promote a healthy lifestyle, including diet, PA, sleep, and mental well-being. Preventive interventions through a holistic, healthy lifestyle may be the solution, considering the inextricable relationship between physical and psychological health. We expect that holistic lifestyle mHealth may effectively support behavioural changes among women with a history of GDM to prevent T2D and CMDs.

**Trial status:**

The protocol study was approved by the National Healthcare Group in Singapore, Domain Specific Review Board (DSRB) [2023/00178]; June 2023. Recruitment began on October 18, 2023.

**Trial registration:**

ClinicalTrials.gov NCT05949957. The first submission date is June 08, 2023.

**Supplementary Information:**

The online version contains supplementary material available at 10.1186/s13063-024-08247-x.

## Introduction

### Background and rationale {6a}

Individuals, families, and societies worldwide are affected by diabetes. According to recent reports, one in ten adults has diabetes worldwide, accounting for 10.5% of the global population [1, 2]. Globally, it is projected to be 700 million people with diabetes, with women being 343 million by 2045 [2]. Diabetes ranks ninth for women and eighth for men in the global ranking of disability-adjusted life years (DALYs) [3, 4]. There is a parallel increase in obesity and type 2 diabetes (T2D) in the general population, as well as a rise in gestational diabetes mellitus (GDM) incidence [5]. GDM affects between 1 and 30% of pregnancies worldwide [6] and is particularly prevalent among Asian women [7], showing distribution in the Middle East (8.8–20.0%), Southeast (9.6–18.3) and Western Pacific (4.5–20.3%), respectively [6]. A recent report in Singapore shows that GDM prevalence is 23.5% [8]. GDM can cause pregnancy and birth complications and long-term chronic conditions such as cardiometabolic disorders and T2D in both mother and offspring [9, 10]. Compared to women with a normoglycemic pregnancy, women with a history of GDM are more likely to develop T2D [11]. The prospective birth cohort study in Singapore, Growing Up in Singapore Towards Healthy Outcomes (GUSTO), showed that the risk of developing T2D is 12-fold higher in Singaporean women 4–6 years after their GDM diagnosis [12].

Risk factors for T2D among those with a history of GDM included greater pre-pregnancy Body Mass Index (BMI), excessive weight gain, unhealthy dietary patterns, physical inactivity, and a short period of lactation [13]. Post-natal risk, such as missing medical assistance in the continuum of GDM care after delivery, could be another risk for progression to T2D among Asian mothers with a history of GDM [7]. In terms of the pathophysiology, GDM has several similarities to T2D, namely impaired insulin sensitivity and dysfunction of the β-cell caused by the metabolic stress of pregnancy [5, 14].

Besides T2D and cardiometabolic diseases, current literature suggests that women with a history of GDM also have a higher risk of developing common mental disorders (CMDs) (depression, anxiety) [15, 16]. CMDs are the most common morbidity in the peripartum (during pregnancy and up to 1 year following delivery). Approximately one in five women develop CMDs during pregnancy or in the year following delivery [17], which is associated with adverse maternal and foetal outcomes as well as emotional and behavioural difficulties in the offspring [18]. Likewise, poor quality of sleep associated with gestational diabetes can pose significant health risks to both mothers and their newborns [19–21]. Previous studies have shown that women with GDM have shorter sleep time, less efficient sleep, and more sleep disorders and daytime dysfunction [19]. The evidence has been demonstrated that sleep disturbances can impair glucose metabolism by affecting insulin sensitivity and β-cell function, which is also associated with obesity and depression [20]. Thus, women with a history of GDM also may present poor sleep quality and CMDs. However, effective interventions that aim to improve these women’s mental well-being and sleep quality remain scarce.

A systematic review and meta-analysis about the prevention of T2D in women with previous GDM has shown that lifestyle interventions produced only a borderline reduction in T2D risk (RR 0.75, 95% CI: 0.55–1.03) [22]. The interventions did not focus on modifiable risk factors like sleep and mental well-being, which could have been addressed to improve the outcome. Observational studies suggest that approximately 45% of GDM cases might be preventable by the adoption of a healthy diet and increased physical activity (PA), including psychosocial factors (stress, anxiety, depression interventions) [6, 23–25]. However, most preventative studies are undertaken in Western countries [21], and it is challenging to directly apply these strategies in Asian countries due to differences in demographics, socioeconomics, ethnicity, and cultural factors [7]. A recent systematic review study concluded that in most of the studies, the evidence-based intervention might not be culturally appropriate for the prevention of T2D in women with a history of GDM [13].

Postpartum women often report difficulty engaging with lifestyle management interventions due to several barriers [26, 27], including multiple face-to-face sessions, travel distances, time constraints, and cost are some factors [26, 28] that may be alleviated by technological advancements [29]. Thus, lifestyle interventions delivered through mobile health (mHealth) interventions represent a feasible, affordable and scalable solution for the prevention of T2D and CMDs among women with a history of GDM [30]. While several mHealth lifestyle intervention studies have been conducted to prevent NCDs [31, 32] and CMDs [33] few have taken a holistic approach to improving health and mental wellbeing. The inextricable link between physical and psychological health [2, 4, 22–24] highlights the combined effects of holistic interventions integrating body and mind may have a greater total effect than any single intervention in preventing T2D and CMD [34]. The LvL UP is a scalable holistic mHealth intervention to prevent NCDs and CMDs in Asian populations [35]. The intervention has been informed by leading evidence- and theory-based frameworks in mental health [36] and behaviour change [36] to deliver motivational interviewing-inspired digital coaching via conversational agent and behavioural tools centred around three core pillars: Move More, Eat Well, Stress Less. The intervention has undergone rigorous development and refinement, including feasibility and user-centred design studies (unpublished data) to assess its technical feasibility and acceptability, but has not yet been tested for effectiveness.

### Objectives {7}

This study aims to assess the effectiveness of a scalable smartphone-delivered holistic lifestyle coaching intervention for the prevention of T2D and CMDs with post-GDM Asian women from the community setting in Singapore. We have five specific objectives:Objective 1: To carry out a 1-year randomised control trial (RCT) followed by a 3-year follow-up period with post-GDM women from the community setting in Singapore.Objective 2: To examine the potential impacts of the proposed intervention on the health and mental well-being of women and their children.Objective 3: To determine the diabetes risk of the participants over a 3-year follow-up period.Objective 4: To explore the potential economic impacts of the proposed intervention (e.g. healthcare expenditures)Objective 5: To study the importance of gut microbiota and epigenetic factors in changes in glucose metabolism.

### Trial design {8}

This study is a 1-year randomised controlled trial (RCT) with 3 years of follow-up. We will conduct a two-arm single parallel assignment individually randomised equal allocation control trial on *n* = 400 women with a history of GDM. It will compare the aggregate effects of the Intervention group (receiving a holistic lifestyle mHealth intervention (LvLUP App), Sleep tracker, Oura ring/Oura App and psychoeducation to promote healthy lifestyle (Happy App)) and (comparison group (Happy App (psychoeducation only), Oura ring and Oura App) at 26/27 weeks, and 1-year visit. After completing the 1-year RCT period, both groups will be followed up in years 2, 3, and 4. We hypothesise that the intervention will reduce the risk of T2D/pre-diabetes and CMDs in post-GDM women.

## Methods: participants, Interventions, and outcomes

### Study settings {9}

Participants are women with a history of GDM from a large community setting in Singapore.

### Eligibility criteria {10}

All eligible females in this study will be (a) women between 21 and 45 years old; (b) with a history of GDM (at least 1 year and no more than 10 years); (c) Chinese, Malay, or Indian ethnicity; (d) BMI between 18.5 and 35 kg/m^2^; (e) not planning to conceive in the next 1 year; (f) not performing exclusive breastfeeding during the study period; (g) owners of a smartphone compatible with the study mobile Apps; (h) proficient in the English language; (j)willing to comply with study protocol; and (k) able to provide written informed consent.

Exclusion criteria include (a) current or previous diagnosis of diabetes (type 1 or 2), except GDM; (b) currently pregnant; (c)given birth within the last 12 weeks; (d) severely limited mobility (e.g. wheelchair-bound, require long-term walking aid, etc.); (e) diagnosed with malnutrition or eating disorder; (f) diagnosed with cancers, unstable heart diseases, severe kidney disease, severe liver disease; (g) diagnosed with severe insomnia, unstable mental conditions, dementia, or cognitive impairment; (h) experienced alcohol or drug abuse; (i) currently having medications known to influence glucose metabolism (e.g. peroral corticosteroids); and (j) currently participating in a concurrent clinical trial or lifestyle intervention study.

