### Criteria for discontinuing or modifying allocated interventions {11b}

The participant will be withdrawn from the study if she becomes pregnant during the 1-year intervention period. If a participant becomes pregnant during the 3-year follow-up period, she will skip the follow-up visit for the year and return to the subsequent follow-up visit(s) post-pregnancy. In the same way, if a participant is diagnosed with T2D by her doctor during the 1-year intervention period, she will be invited to complete the endpoint study visit measures before being withdrawn from the study. If the participant is diagnosed with T2D by the study team during the follow-up visits, she will be removed after completing that visit.

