### Relevant concomitant care permitted or prohibited during the trial {11d}

The participants will be excluded if they have enrolled in a concurrent lifestyle intervention research study during the study. However, trial participants can receive concomitant treatment (e.g. psychotherapy, pharmacology), which will be assessed during the follow-up period.

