## Assignment of interventions: blinding

### Who will be blinded {17a}

Given the nature of the study design, blinding of participants and research personnel will not be possible. The study team will instruct the participants in the intervention and comparison groups to download the Apps, and each participant will be provided with a unique identification code.

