## Statistical methods

### Statistical methods for primary and secondary outcomes {20a}

#### Analysis of aggregate intervention effects

The primary continuous outcome for the onset of diabetes will be analyzed with linear mixed models (LMM) with outcome measurement (at the three follow-up time points) as the dependent variable and based on the intention-to-treatment (ITT) principle.

Multiple linear regressions will determine the relationship between outcome measures and predictors, adjusting for potential confounders. Multiple linear regression analyses will estimate the effects between groups at the end point follow-up. Generalised estimating equations and mixed effect models will be used for longitudinal data analysis. A *p*-value of < 0.05 will be considered statistically significant. Correction for multiple tests will be performed. All statistical analyses will be conducted using the R program or STATA for Windows (Stata Corporation). The treatment effect within and between the two groups will be assessed using the Cohen *d* statistics [65].

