### Methods in analysis to handle protocol non-adherence and any statistical methods to handle missing data {20c}

Intention-to-treat analysis will be used to examine trial efficacy. Total scores will be modelled using fixed effects of time, intervention group, interaction between time and intervention group, and a random effect of individual.

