Biological samples will be collected through blood tests, which will be analyzed by an accredited lab providing the normal reference range of the lab results. The PI ([name]) will review blood test results. For all abnormal blood test results and incidental findings discovered during the study period, the study PI will determine if the findings are clinically significant and actionable. The study PI will sign a referral letter to seek primary healthcare. Subsequently, a delegated study team member will contact the participant to relay the internal findings on behalf of the study PI. Participants who agree to be re-identified and notified of the internal findings will be contacted at their primary contact number provided in the consent form. The referral letter will be emailed to her. If the participant is uncontactable on her direct contact number, her next of kin listed on the consent form will be contacted. If the participant and next of kin are not contactable after 1 month, the referral letter will be sent directly to the participant’s home address. In the case incidental findings meet the study exclusion criteria, the affected participant will be informed and withdrawn from the study.

For the rest of the study measures/questionnaires, there is no clinical validation available. Hence no applicable management plan will be carried out.

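### Section {11d}, as worded, excludes randomised women who later join another lifestyle study; it is not among the discontinuation criteria in {11b} and conflicts with intention-to-treat unless follow-up and analysis are retained

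*Protocol article*

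**What the plan says.** Five places in the protocol article bear on this point.

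- **Eligibility criteria {10}, exclusion (j).** A woman is ineligible if she is "currently participating in a concurrent clinical trial or lifestyle intervention study". This is an entry rule.
- **Concomitant care {11d}, first sentence.** "The participants will be excluded if they have enrolled in a concurrent lifestyle intervention research study during the study". This concerns conduct during the trial. It names lifestyle studies only, whereas {10} also names clinical trials.
- **Concomitant care {11d}, second sentence.** By contrast, "trial participants can receive concomitant treatment (e.g. psychotherapy, pharmacology), which will be assessed during the follow-up period". These treatments are recorded and are not a ground for exclusion.
- **Discontinuation criteria {11b}.** The listed reasons are pregnancy ("The participant will be withdrawn from the study if she becomes pregnant during the 1-year intervention period") and a diagnosis of type 2 diabetes. Joining another study is not listed.
- **Analysis.** Section {20a} says that the primary outcome is analysed "based on the intention-to-treatment (ITT) principle". Section {20c}, on non-adherence and missing data, says "Intention-to-treat analysis will be used to examine trial efficacy".

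Two further statements give context. Section {17a} says that "blinding of participants and research personnel will not be possible". Section {22} applies exclusion criteria after entry in another setting and says what follows: "In the case incidental findings meet the study exclusion criteria, the affected participant will be informed and withdrawn from the study".

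**The concern.** Whether a woman joins another lifestyle study after randomisation is something that happens after allocation and may depend on it. She knows her arm. The comparison arm receives educational content and tracking, while the intervention arm also receives coaching, prompts and payment for completed coaching levels. If joining another study ends a woman's follow-up, the women left in each arm are no longer simply those whom randomisation put there.

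Two things are at stake. The first is possible selection: women who look for another study may have a diabetes risk above or below that of the others, and the proportion who do so may differ between arms. The second is avoidable loss of glucose tolerance tests and questionnaires from women who may be willing to keep attending.

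There is also a practical problem. Staff who follow {11b} would keep such a woman in the study, and staff who follow {11d} would exclude her. That choice would be made by people who know her arm.

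**Working it through.** **1. What the text does and does not settle**

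| Question | {10}(j) | {11b} | {11d} | {20a}, {20c} |
|---|---|---|---|---|
| When does it apply? | At entry | After randomisation | During the study | At analysis |
| Is joining another study named? | Yes, if current | No | Yes, lifestyle research studies only | No |
| Consequence | Not enrolled | Withdrawn or removed | Excluded, with no statement from what | Intention-to-treat |

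Sections {10} and {11d} govern different stages and do not contradict each other. The tension lies between {11d} and {11b}, and between {11d} and the analysis sections.

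**2. The plan's own figures (Sample size {14})**

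Inputs: hazard ratio 0.5, power 80%, median 6 years in the comparison group, 3 years of follow-up, 20% censoring. The significance level is printed as 0.05%, but the stated events are reproduced only with 0.05 two-sided, which I use.

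- Events (Schoenfeld) = 4 × (1.960 + 0.842)² / (ln 0.5)² = 65.3. The plan states 65.
- Event hazards are ln 2 / 6 = 0.1155 per year in the comparison arm and half of that in the intervention arm. Reading the 20% as a censoring hazard c = 0.20 per year, P = λ/(λ+c) × [1 − exp(−3(λ+c))] = 0.224 and 0.121. The plan states 0.22 and 0.12.
- N = 65 / mean(0.224, 0.121) = 377. The plan states 189 + 188 = 377.

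The plan's figures are thus reproduced, and its event rates already contain an allowance for censoring.

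**3. Effect on numbers**

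The article gives no rate of joining other studies, so the removal rates here are assumptions. With 400 randomised and a mean event rate of (0.22 + 0.12)/2 = 0.17:

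| Removed from both arms | Expected events | Power at HR 0.5 |
|---|---|---|
| 0% | 400 × 0.17 = 68.0 | 81.5% |
| 5% | 380 × 0.17 = 64.6 | 79.5% |
| 10% | 360 × 0.17 = 61.2 | 77.4% |

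The loss of power is small.

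**4. Effect on the estimate**

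Assume that a fraction p of the comparison arm is removed and none of the intervention arm, and that removed women have r times the risk of those retained. The arm's overall risk is 0.22, so the risk in the retained women is 0.22 / (1 − p + p·r). With no true effect, the intervention arm's risk is also 0.22, and the apparent risk ratio is 1 − p + p·r. The planned ratio is 0.12/0.22 = 0.545.

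| p | r | Retained comparison risk | Apparent ratio, no true effect | Apparent ratio, planned effect |
|---|---|---|---|---|
| 0.05 | 0.5 | 0.22/0.975 = 0.2256 | 0.975 | 0.532 |
| 0.05 | 1.5 | 0.22/1.025 = 0.2146 | 1.025 | 0.559 |
| 0.10 | 0.5 | 0.22/0.950 = 0.2316 | 0.950 | 0.518 |
| 0.10 | 1.5 | 0.22/1.050 = 0.2095 | 1.050 | 0.573 |

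On the hazard ratio scale, ln(1 − 0.12)/ln(1 − 0.22) = 0.51 becomes 0.49 (p = 0.10, r = 0.5) or 0.54 (p = 0.10, r = 1.5).

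**5. Type I error**

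With 65 events, SE(log HR) = 2/√65 = 0.248. Taking the log of the apparent risk ratio as the shift, at p = 0.10 and r = 0.5 the shift is ln 0.95 / 0.248 = −0.207 standard errors. The two-sided error is then Φ(−1.753) + Φ(−2.167) = 0.040 + 0.015 = 0.055. At p = 0.05 and r = 0.5 it is 0.051. At p = 0.10 and r = 1.5 it is 0.054, with the shift against the intervention. Converting the risks to a hazard ratio first gives 0.056 at p = 0.10 and r = 0.5.

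**The case against.** The strongest reply is that {11d} does not say from what a woman is excluded. She could stop taking part and still be analysed as randomised, so no contradiction with intention-to-treat is proven. Where the article clearly removes women it speaks of withdrawal or removal, and {11d} uses neither word. The sentence might be a loose restatement of the entry rule. A ban on concurrent lifestyle trials also protects the contrast under test, and {11d} is the natural place for one. Details of follow-up and analysis sets may stand in the full protocol or the analysis plan.

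Much of this stands. The conflict with intention-to-treat is conditional, and I state it so. What does not stand is that the point is merely a missing detail. The article states a rule, places it under care during the trial, and ties it to enrolment while the study is running, which favours a reading after randomisation. If only the entry rule was meant, the sentence still needs correcting.

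A reader might go further in three ways that the documents do not support.

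- **That the bias favours LvL UP.** One can argue that motivated, lower-risk women would leave the comparison arm. But the HAPPY App shows both arms their glucose results, so women whose results worsen might equally be the ones who look elsewhere. The one-sided conclusion follows only if r is fixed below 1; at r = 1.5 it reverses. Nothing in the article states or quantifies a difference by arm.
- **That exclusion runs for the whole 4 years and that later data are lost.** The article states neither. It separates the 1-year trial from the follow-up without saying to which the rule applies.
- **That any outside programme triggers it.** The sentence covers lifestyle intervention research studies only. Gyms, commercial apps and dietitians fall outside it, so the trigger is narrow and 10% of an arm may well be generous.

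The calculation also treats each woman as removed at randomisation. Real exclusions would come later, after some tests had been done, so for a given p and r the figures lean high.

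**Conclusion.** The point holds in a limited form. Read plainly, {11d} excludes women for what they do after randomisation, is not matched in {11b}, and conflicts with {20a} and {20c} unless follow-up and analysis are retained. If it is applied as loss of follow-up, removal may be informative and may differ by arm, in an unknown direction and at an unknown rate.

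Under the assumptions above (up to 10% removed from the comparison arm only, at 0.5 to 1.5 times the risk of the rest), the distortion is about 5% in the risk ratio either way, with type I error near 5.5%. The expected harm is modest. The case for acting is that the rule is unclear, that its application would rest with unblinded staff, and that the cost of clarity is close to nil. The 20% censoring allowance can absorb lost numbers, but it does not correct informative removal.

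**What to change.** - Keep exclusion (j) in {10} as an entry criterion only.
- Reword {11d} so that a woman who enrols in another lifestyle study after randomisation stays in scheduled follow-up and in the intention-to-treat analysis as randomised.
- Bring {11b} into line with {11d}, so that staff have one rule.
- Record the enrolment and its date at each visit and report both by arm. Section {11d} already treats psychotherapy and drug treatment in this way.
- Optionally, add a sensitivity analysis that censors at the date of enrolment in the other study. Such censoring may itself be informative, so it should support the main analysis and not replace it.

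The change concerns follow-up and analysis. It does not touch what a woman may use or receive in either arm.

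The cost is one sentence and one recorded item per visit. The screening survey already asks about fitness or wellness programmes, and Table 1 repeats the lifestyle survey at year 1. The drawback is that a few women with a co-intervention remain in the primary analysis and may slightly dilute the contrast; the sensitivity analysis would indicate by how much.
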